#### Selection of Investigators

This study will be conducted at a tertiary-level public hospital’s department of cardiology. Investigators will be the authors of this publication and other staff based at Tygerberg Hospital.

### Statistical Considerations

#### Sample Size

We determined that a target number of 248 primary outcome events would provide a power of 80% to detect a 30% lower relative risk of the primary outcome in the novel sequencing arm than in the conventional sequencing arm at a 2-sided α level of .05. Assuming an incidence of the primary outcome of at least 50% over 5 years in the conventional sequencing arm and a dropout of 10% per arm, we established a planned enrolment of 584 patients (292 per study arm).

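### The planned 584 patients match the no-dropout figure, and the 30% effect appears to be used on two scales; at a hazard ratio of 0.70 the power is 77.6% to 79.9%, not 80%.

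*Protocol article*

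**What the plan says.** The Sample Size section of the protocol article gives the event target as follows: "a target number of 248 primary outcome events would provide a power of 80% to detect a 30% lower relative risk". The test is set "at a 2-sided α level of .05". The enrolment sentence opens with the control-arm premise: "Assuming an incidence of the primary outcome of at least 50% over 5 years in the conventional sequencing arm". Dropout and the resulting number come next in that sentence: "a dropout of 10% per arm, we established a planned enrolment of 584 patients (292 per study arm"). No intermediate figure is shown: neither the assumed risk in the novel arm nor the step that allows for dropout.

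Other sections bear on the calculation:
- The Abstract (Methods) gives 5 years of follow-up for participants.
- Selection of Patients gives a recruitment period of 1 year.
- Table 1 names Cox regression for the primary components, at the end of the trial, under a hypothesis that runs from baseline to 5 years.
- Analysis Population keeps the data of participants who drop out, but does not say whether their events after leaving will be sought.

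**The concern.** The section gives every input, says that dropout was among them, and fixes a result. A reader should be able to get from the inputs to 584. The simplest route does reach 584, but only with the dropout term left out. That route also needs a different meaning of the 30% reduction from the one that produces 248 events.

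At stake is whether the event target, enrolment, dropout and power can hold together, and which effect the trial is powered to detect. This is the only sample-size justification in the document, and it will support the funding request and the ethics application, neither of which is complete according to the Results section.

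**Working it through.** **Inputs (Sample Size section unless noted).** Events D = 248; power 80%; two-sided α 0.05; 30% reduction; control risk 50% at 5 years (the stated minimum); dropout 10% per arm; N = 584, 1:1. Follow-up of 5 years is from the Abstract. Constant hazards are my assumption.

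**1. The event target reproduces at a hazard ratio (HR) of 0.70.** Schoenfeld: D = 4(1.960 + 0.842)² / (ln 0.70)² = 246.8, so 247. With 248 events, power is 80.2%.

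**2. Enrolment reproduces without dropout.** If the 30% is a ratio of 5-year risks, the novel arm has 0.70 × 50% = 35%, and the mean risk is (50% + 35%)/2 = 42.5%.
- No dropout: 248 / 0.425 = 583.5, so 584, or 292 per arm. This is the stated figure.
- 10% contributing nothing: 248 / 0.425 / 0.9 = 648.4, so 649.

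**3. The two scales differ.**
- HR 0.70 from a 50% control risk gives a novel-arm risk of 1 − 0.5^0.7 = 38.4% and a mean of 44.2%. Then 248 / 0.4422 = 561 without dropout, and 248 / 0.4422 / 0.9 = 623.1, so 624 with it. Neither is 584.
- 50% against 35% is HR = ln 0.65 / ln 0.50 = 0.62, for which 80% power needs only 4(1.960 + 0.842)² / (ln 0.6215)² = about 139 events, not 248.

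**4. What 584 patients deliver at HR 0.70 throughout, 5 years each.** Power = Φ(|ln 0.70| × √D / 2 − 1.96).
- *Dropouts contribute nothing.* D = 584 × 0.9 × 0.4422 = 232.4. Power = Φ(2.719 − 1.960) = 77.6%.
- *Dropouts count until they leave.* Take a constant dropout hazard γ reaching 10% at 5 years: γ = −ln 0.9 / 5 = 0.0211 per year. Event hazards are λ = ln 2 / 5 = 0.1386 (control) and 0.7 × 0.1386 = 0.0970 (novel). The chance of an observed event is λ/(λ+γ) × (1 − exp(−5(λ+γ))), which is 47.7% and 36.6%. D = 292 × (0.4774 + 0.3664) = 246.4. Power = 79.9%.

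**5. What would close the gap at HR 0.70, even with the full 10% loss.**
- *Higher control risk.* At 52% the events are 242 and at 54% they are 252, so a control risk of about 54% is enough.
- *Longer follow-up.* Suppose uniform entry over the 1-year recruitment and a common close 5 years after the last entry, so 5 to 6 years each. Mean risks are 53.3% and 41.3%, average 47.3%. D = 584 × 0.9 × 0.4732 = 248.7, power 80.3%, and required N = 248 / 0.4732 / 0.9 = 582.
- *The reverse case.* A close 5 years after the first entry (4 to 5 years each) gives about 215 events and 74% power.

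**The case against.** The best defence is the common-close reading in step 5. It uses the document's own recruitment period, takes the full 10% loss, keeps one scale (HR 0.70), and needs 582 patients, very near 584. Table 1 places the primary components at the end of the trial, which fits. The arithmetic stands, so the figures could be made consistent. But no section states that closing rule. The Abstract's 5-year follow-up, the 5-year incidence in the sample-size sentence and the baseline-to-5-years hypothesis in Table 1 all read more naturally as 5 years per participant. A different unstated closing rule would make matters worse.

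Three further points have weight:
- The 35% and 42.5% are inferred from the match with 583.5 and are not printed in the document. A 30% lower relative risk is also common loose wording for HR 0.70. So the omission of dropout and the use of two scales are the most likely explanation, not a documented fact.
- The 50% control risk is stated as a minimum, and a modestly higher risk removes the shortfall.
- Dropouts' data are to be analysed, and Cox regression uses time before censoring, so total loss of their information is the pessimistic end. If their events were fully ascertained after they left, nothing would be lost, but then the dropout assumption would have no role in the sentence.

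A reader might go further and infer that power falls to about 76%, from 584 × 0.9 × 0.425 = 223 events, or that about 650 patients must be enrolled. The documents do not support that. The 76% takes its events from 50% against 35%, which is HR 0.62, but its power from HR 0.70. If 50% against 35% were true, 223 events would give about 94% power.

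**Conclusion.** The point holds in limited form. The stated 584 does not follow from the stated inputs over 5 years: it equals the no-dropout figure, and the 30% reduction appears to mean a hazard ratio for the events and a risk ratio for the enrolment.

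The consequence is small. At HR 0.70, 50% control risk, constant hazards and 5 years each, the trial yields about 232 to 246 events against 248, and 77.6% to 79.9% power. The shortfall is therefore between 0.1 and 2.4 points. It disappears with a control risk of about 54%, or with a common close 5 years after last entry.

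This is an inconsistency to correct, not evidence that the trial is seriously underpowered or must be enlarged. Severity: should-fix.

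**What to change.** State the effect once, as a hazard ratio of 0.70, with the 5-year risks it implies (50% and 38.4%), and show how the 10% dropout enters. Then choose one of two forms:

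1. *Fixed 5 years each.* Restate the section as 584 enrolled with 10% loss, giving about 232 to 246 events and about 78% to 80% power, depending on whether dropouts contribute follow-up until they leave. The cost is a slightly lower stated power.
2. *Keep 584 and 80%.* State that the final analysis takes place at the 248th event, or at a common close 5 years after the last entry, and align the Abstract and Table 1 with that rule. The cost is slightly longer follow-up.

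Neither needs extra patients. Since funding and ethics approval are still to come, the change is a matter of rewording.

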#### Analysis Population

The analysis population will include all study participants included in the study. This is an intention-to-treat analysis and even participants who have withdrawn, or dropped out, from the study after randomization will have their data analyzed.

#### Statistical Methods

Patient demographic and clinical profiles will be described using the statistical software SAS (version 9.4; SAS Institute). Continuous variables will be expressed as an absolute number, with associated percentage, mean, SD, median, and range where applicable. Clinical assessment of response to heart failure therapy will be performed using the Kansas City Cardiomyopathy Questionnaire, New York Heart Association functional classification, 6-minute walk distance, and hospital admission for heart failure. Objective measures of therapy response will be ascertained by serial N-terminal prohormone of brain natriuretic peptide levels and 2D echocardiography. Echocardiographic features of response to therapy will be characterized according to left ventricular ejection fraction as determined by the Simpson biplane method, global longitudinal strain, and speckle tracking.

Associations between outcomes and indicator variables will be explored through logistic regression. Where appropriate, indicator variables and specific outcomes will be investigated individually through a univariate analysis. Where significant, variables will be entered into and controlled for in a Cox-proportional hazards regression model. Adjustment for confounding will be performed by a competing risks analysis and propensity score matching (Table 1).

**Table 1 table1:** Statistical methods.

Outcome measures		Hypothesis	Measure	Time points	Analysis methods
**Primary** **end points**		The intervention will reduce the outcome from baseline to 5 years.	—^a^	—	—
	All-cause mortality	Rapid sequencing of anti–heart failure therapy will reduce all-cause mortality.	All-cause mortality (binary)	End of trial	Cox proportional hazards regression
	Hospitalization	Rapid sequencing of anti–heart failure therapy will reduce all-cause mortality.	Hospitalized for heart failure (binary)	End of trial	Cox proportional hazards regression

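### The Statistical Methods text prescribes propensity score matching, competing-risks analysis and significance-screened covariates to adjust a randomized comparison, which conflicts with the intention-to-treat population and leaves the primary model unfixed

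*Protocol article*

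**What the plan says.** All places are in the Protocol article.

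- **Selection of Patients:** arms are allocated from a computer-generated randomization sequence.
- **Analysis Population:** the analysis is by intention to treat and covers everyone in the trial; patients who leave once randomized stay in the analysis.
- **Statistical Methods, text:** outcomes and unnamed indicator variables are explored by logistic regression and univariate analysis. Then: "Where significant, variables will be entered into and controlled for in a Cox-proportional hazards regression model". The next sentence, which points to Table 1, reads: "Adjustment for confounding will be performed by a competing risks analysis and propensity score matching".
- **Statistical Methods, Table 1:** Cox regression is the method for both primary rows, all-cause mortality and hospitalization. There is no row for the composite. Cardiovascular death is assigned a chi-square test.
- **Primary Objective:** the primary end point is the composite of all-cause mortality and heart failure hospitalization.

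No section labels the matching, the competing-risks analysis or the screened model as sensitivity, secondary or exploratory.

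**The concern.** This is an analysis plan for an observational cohort attached to a randomized trial, and four things go wrong.

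1. Randomization removes systematic confounding by arm. Chance imbalance remains, but the test already allows for it, and baseline covariates fixed in advance deal with it better than matching does.
2. Matching as usually done keeps only patients who find a partner within a caliper. It cannot share a comparison with a population defined as everyone randomized.
3. Competing-risks methods deal with events that preclude the event of interest. They do not adjust for confounding. Because death from any cause is part of the primary composite, no competing death is left.
4. The Cox model is chosen by tests against the outcome. Nothing restricts the indicator variables to baseline measurements, so a variable measured after randomization, and possibly affected by the sequencing strategy, could enter the model and bias the treatment effect. Logistic screening also ignores follow-up time over 5 years.

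At stake is which number the trial reports as its result. Unadjusted, screened and matched estimates are all allowed by the text, and nothing ranks them.

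**Working it through.** **Inputs from Sample Size.** "a target number of 248 primary outcome events"; "would provide a power of 80% to detect a 30% lower relative risk of the primary outcome"; significance "at a 2-sided α level of .05"; "incidence of the primary outcome of at least 50% over 5 years in the conventional sequencing arm"; 584 patients, 292 per arm.

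**Step 1: reproduce the plan's figure.** Schoenfeld events for 1:1 allocation: 4 × (1.960 + 0.842)² / (ln 0.70)² = 246.8, so 247. Freedman's formula gives 253. The stated 248 is reproduced. Power with 248 events = Φ(√248 / 2 × |ln 0.70| − 1.960) = 80.2%. For patients: 248 / ((0.50 + 0.35) / 2) = 583.5, so 584.

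**Step 2: how many patients matching drops.** The plan gives no ratio, caliper, algorithm or covariate list, so these are assumptions: 292 per arm, independent baseline covariates, greedy 1:1 matching without replacement on the logit of the propensity score. With six covariates:

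| Caliper (SD of logit) | Randomized patients dropped |
|---|---|
| 0.1 | 15% |
| 0.2 | 11% |
| 0.5 | 8% |
| 1.0 | 6% |
| none, equal arms | 0% |

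At a caliper of 0.2 SD, the mean number dropped was 64 of 584 (11%) with 5 covariates, 75 (13%) with 10 and 83 (14%) with 15. There was no confounding in these data to remove.

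**Step 3: power by formula.** Assume events fall in proportion to patients:

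| Share kept | Events | Power at HR 0.70 |
|---|---|---|
| 100% | 248 | 80.2% |
| 95% | 236 | 78.2% |
| 90% | 223 | 75.9% |
| 85% | 211 | 73.5% |

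**Step 4: power and type I error by simulation, caliper 0.2 SD.**

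- *Simulation A:* six covariates with log hazard ratios 0.35, 0.35, 0.25, 0.20, 0.15 and 0.10; baseline hazard 0.128 per year; 10% dropout at 5 years; 4,000 trials per scenario.
- *Simulation B:* ten covariates, three of them prognostic (0.5, 0.3, 0.2); baseline hazard ln 2 / 5 per year; no dropout; 400 trials at HR 0.70 and 800 under no effect.

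| Analysis | A: power | A: null | B: power | B: null |
|---|---|---|---|---|
| Unadjusted Cox | 71.1% | 4.5% | 74.5% | 5.4% |
| Matched | 67.8% | 3.3% | 69.0% | 2.8% |
| Cox, six fixed covariates | 79.0% | 4.9% | – | – |
| Cox, significance-screened | – | – | 82.5% | 5.5% |

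Matching against unadjusted costs 71.1 − 67.8 = 3.3 points in A and 74.5 − 69.0 = 5.5 points in B. In B under no effect, at least one of the three analyses was significant in 8.4% of trials. Monte Carlo standard errors in B are about 2 points for power (√(0.745 × 0.255 / 400) = 0.022) and 1 point or less for the null rates (√(0.084 × 0.916 / 800) = 0.010).

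**Step 5: competing risks, by end point.**

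- Composite of all-cause death and heart failure hospitalization: no competing death, because every death counts.
- All-cause death alone: none.
- Heart failure hospitalization alone: death competes, so the method is relevant.
- Cardiovascular death: other deaths compete, but Table 1 plans a chi-square test.

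**The case against.** The strongest reply is that Table 1 names Cox regression, and neither matching nor competing risks, for both primary rows. The text before it speaks of exploring associations, so the contested sentences may describe predictor work beside the trial comparison. This part stands: a reader might infer that the primary estimate will come from a matched subset, and the document does not say so. What can be said is that the role of these analyses is not stated.

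Three further inferences are tempting and not supported.

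- *The matched set is a post-hoc subset.* Matching is announced in advance, and a propensity score is normally built on baseline variables, not on outcomes.
- *Screening inflates type I error.* For true baseline covariates it did not: 5.5% against 5.4% unadjusted. The 8.4% arises only if any of three analyses may be claimed. The document does not plan that, although it does not exclude it. The objection to the screen is that it leaves the model open and is not limited to baseline variables.
- *Deleting the matching raises power to 79%.* That figure comes from adding six covariates of assumed strength. Dropping the matching alone recovers about 3 to 6 points.

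It is also true that matching without a caliper in equal arms drops nobody, that the matched analysis was conservative rather than anti-conservative, and that competing-risks methods have a proper place for the hospitalization row. A covariate list can be left to an analysis plan that is not shown. However, such a plan could not reconcile matching as a confounding adjustment with the stated analysis population. That wording is in this document and has to be changed here.

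**Conclusion.** The point holds as a fault in what the protocol states, not in what it omits. Matching and competing-risks analysis are given a task that randomization has already done and that the second cannot do. Under usual caliper matching, about 6% to 15% of randomized patients would be excluded, against the protocol's own analysis population, at a cost of roughly 3 to 6 points of power. These sizes depend on the assumed caliper, matching algorithm and covariates, and the loss is zero without a caliper in equal arms.

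The loss of power is modest. The larger fault is that the treatment comparison is not pinned to one model. Several adjusted answers are available, none is ranked, and the screened variables need not be baseline measurements.

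**What to change.** 1. Delete the propensity score matching and the wording about adjusting for confounding, or keep matching only as an analysis labelled exploratory.
2. Drop significance-based selection of variables for the treatment comparison. If predictors of outcome are of interest, describe that as separate exploratory work.
3. State one primary analysis: Cox regression for time to the first of all-cause death or heart failure hospitalization, in all randomized patients, and add this composite as a row of Table 1. Make it either unadjusted or adjusted for a short list of baseline covariates fixed in advance, and show the other version beside it. NYHA class, ejection fraction and NT-proBNP, which Table 1 measures at baseline, are possible choices. No particular list is required to cure the fault.
4. Confine competing-risks methods to heart failure hospitalization alone. Extend them to cardiovascular death only if the chi-square entry in Table 1 is changed to match.

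**Cost:** wording only. The Results section says that funding is still being sought and that the ethics application will follow, so no patient is affected. The downside is that the matched analysis is lost or becomes exploratory.

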### Study Objectives

#### Primary Objective

The primary efficacy end point is the composite end point of all-cause mortality and hospitalization for heart failure.

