## Discussion

### Principal Findings

This study aims to determine if rapid sequencing of anti–heart failure drugs with proven morbidity and mortality benefits would be superior to slower titration of these therapies.

We chose a composite end point to reduce the sample size, as a larger sample size would result in greater costs and reduce the feasibility of the study. Given the high mortality and frequent hospitalizations for heart failure, we included both events in the combined primary efficacy endpoint.

Intuitively, it makes sense to ensure that the most efficacious heart failure therapies are initiated as soon as possible. Given that the therapies have varied modes of action, we hypothesize that if they are started together as soon as possible, they would have greater benefits than starting them later. Combination therapies are likely to target different pathophysiological aspects of heart failure and thus improve clinical outcomes. Issues with rapid initiation may potentially include hypotension and other adverse effects. We will guard against hypotensive events by starting with the lowest possible dose and stopping the drug if the patient becomes hemodynamically unstable. Furthermore, study participants are required to be euvolemic before rapid sequencing so that we do not worsen patients’ heart failure and thus limit hemodynamic instability and decompensated heart failure. It is a standard clinical practice to ensure euvolemia before titration of anti–heart failure therapies. Euvolemia is usually achieved by loop diuretics [8].

We chose a relatively young group of patients so that underlying issues such as ischemic heart disease are less probable and would not serve as confounders. Furthermore, this group of patients may benefit from the increased life expectancy as compared with the older group.

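### The trial defines and powers one composite primary end point, but Table 1 assigns the primary analyses to its two components separately and gives the composite none

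*Protocol article*

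**What the plan says.** Three places in the protocol article treat the primary outcome as a single composite:

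- Primary Objective: "The primary efficacy end point is the composite end point of all-cause mortality and hospitalization for heart failure".
- Sample Size: "a target number of 248 primary outcome events" is set for 80% power "to detect a 30% lower relative risk of the primary outcome", with one two-sided alpha of .05 that is not divided.
- Discussion, Principal Findings: "We chose a composite end point to reduce the sample size", and "we included both events in the combined primary efficacy endpoint".

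Table 1 under Statistical Methods is built differently. Its primary heading is plural. The heading row holds a general hypothesis about the outcome over 5 years, but shows a dash (not applicable) for measure, time point and analysis method. Two rows follow. The first has the measure "All-cause mortality (binary" and the second "Hospitalized for heart failure (binary". Each is assessed at the end of the trial by its own Cox proportional hazards regression. The hypothesis cell of the hospitalization row repeats the one for all-cause mortality. No row of the table, and no sentence elsewhere in the article, assigns an analysis to the composite.

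**The concern.** Table 1 is the only place that ties an end point to a method. An analyst who follows it fits two Cox models, one per component, and never makes the comparison for which the trial is sized. An analyst who follows the Primary Objective fits one model, to the composite. The two routes can lead to different conclusions about the trial, and the article does not say which governs.

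The role of the components is also left open. Under a primary heading they could be co-primary (both must succeed), alternative primaries (either suffices), or just the parts of the composite. Each reading has different consequences for error control and power. If the choice is left until results are known, it will be hard to defend as prespecified.

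**Working it through.** **1. Does the sample size belong to the composite?** Inputs from the Sample Size section: 30% reduction (taken as hazard ratio 0.70), 80% power, two-sided alpha .05, equal arms. Schoenfeld's formula:

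events = 4 × (1.960 + 0.842)² / (ln 0.70)² = 4 × 7.849 / 0.1272 = 246.8, so 247.

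The stated 248 events give 80.2% power (79.4% by Freedman's formula, which asks for 253 events). The plan's figure is therefore reproduced, and it fits one test of one outcome at an undivided alpha of .05.

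**2. What does each place specify?**

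| Place | Primary outcome | Analysis |
|---|---|---|
| Primary Objective | one composite | not given there |
| Sample Size | one primary outcome, 248 events | one two-sided alpha of .05 |
| Discussion | one combined end point | not given there |
| Table 1 | mortality and hospitalization in separate rows | one Cox model each, none for the composite |

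**3. Error rate if both Table 1 rows were tested at .05.** This depends on a success rule that the protocol does not give.

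- *Either suffices.* With independent tests, 1 − 0.95² = 9.75%. With correlated tests, 1 − P(|Z₁| < 1.96 and |Z₂| < 1.96) under a bivariate normal gives 9.5%, 9.1%, 8.3% and 7.0% at correlations of 0.3, 0.5, 0.7 and 0.9. The correlations are assumed.
- *Both must succeed.* Alpha does not rise above .05, but the power to win on both cannot exceed the smaller of the two component powers.

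**4. Power of a component tested alone.** The article gives no component risks, so the 5-year control risk p is assumed. The hazard ratio of 0.70 is also an assumption here, because the protocol states it only for the composite. With 584 enrolled and 10% lost, 584 × 0.90 / 2 = 262.8 patients per arm contribute:

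events = 262.8 × [p + 1 − (1 − p)^0.7]

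power = Φ(√events × |ln 0.70| / 2 − 1.96)

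| Outcome | Control risk p | Events | Power |
|---|---|---|---|
| Component | 20% (assumed) | 91 | 40% |
| Component | 30% (assumed) | 137 | 55% |
| Component | 40% (assumed) | 184 | 68% |
| Composite | 50% (Sample Size section) | 232 | 78% |

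The right comparator for the component rows is the 78% in the last line, since all four lines allow for the same losses. The protocol's 80% rests on the full 248 events.

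**The case against.** The strongest defence is that Table 1 merely itemizes the parts of the composite and leaves out the composite's own row. The heading row carries a single hypothesis about one outcome, and the Primary Objective, Sample Size and Discussion are consistent with one another. That probably is the intent. It does not rescue the table: the heading is plural, each component has its own measure and Cox regression, and the composite has neither. Nor is this detail that an article leaves to an analysis plan, because the article does specify primary analyses and they do not match its own primary end point.

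Low component power is also no defect in itself. The Discussion gives sample size as the reason for choosing a composite. It matters only if the components are tested as primaries, as Table 1 has it.

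Two stronger criticisms might be inferred from the same rows, and the document does not support them:

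- *That a binary outcome cannot go into a Cox model.* The measure column lists variable types, and binary can simply mean the event indicator. Naming Cox regression and setting a target number of events both imply event times. The wording is loose, not wrong.
- *That the hospitalization model censors deaths.* Table 1 states no censoring rule, and Statistical Methods plans a competing-risks analysis. That analysis is described as an adjustment for confounding and is not tied to hospitalization, so its role needs stating, but a faulty rule cannot be read into the text.

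The mortality hypothesis in the hospitalization row looks like a copying slip. It needs correcting but carries no statistical weight.

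**Conclusion.** The point stands as an internal contradiction in the primary analysis. The protocol defines and powers one composite, and its table of methods analyses two components and not the composite. This rests on the text alone and needs no assumption.

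A reader might go further and conclude that the type I error rate is uncontrolled. That does not follow. The 7% to 9.8% applies only if success on either component makes the trial positive, and no such rule is stated; if both had to succeed, alpha would hold and the cost would be power. What can be said is that error control is not established for the primary section of Table 1 as it stands.

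The component powers of 40% to 68%, against 78% for the composite, illustrate size only. They depend on the assumed control risks and a common hazard ratio of 0.70. The direction is firmer: no more patients can have a given component than have the composite, so at equal hazard ratio and equal follow-up a component's power cannot exceed the composite's.

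**What to change.** In Table 1:

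1. Replace the two primary rows with one: time from randomization to first heart failure hospitalization or death from any cause, Cox regression, two-sided alpha .05.
2. List all-cause death and heart failure hospitalization as secondary components.
3. Tie the competing-risks analysis already mentioned in Statistical Methods to hospitalization, with death as the competing event.
4. Correct the hospitalization hypothesis so that it refers to hospitalization.

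This restores what the Primary Objective, Sample Size and Discussion already say. It costs a table edit and a few words, and no change in sample size is needed on this account. The Results section reports that funding is still being sought and that ethical clearance will follow, so the correction can be made before any patient is enrolled.
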